### Contamination

In order to assess the extent of contamination between arms, at T1 participants from the treatment arm will be asked several structured questions about the extent to which they shared information and materials about the treatment received with others in the community, and participants from the waitlist arm will be asked about whether they have heard about the other treatment and materials from others. This information will be used descriptively to determine contamination.

### Analysis

All analyses will be detailed in a statistical analysis plan, which will be signed before unmasking the study data set. Data will be downloaded from the Kobo data collection software and imported into statistical analysis software for data management and analysis. Details of data security and storage can be found in ethical protocols, which are available on request. Data will be co-owned by the PIs’ organisations, data sharing agreements will be signed by all organisations and co-investigators, and data will be made available on request. All study team members meeting criteria for authorship will be invited to co-author papers presenting the findings.

To determine comparability between the conditions at baseline, multiple planned comparisons will be conducted for continuous variables and chi-squared tests for categorical ones; significance testing will be adjusted for multiple comparisons.

An intent-to-treat analysis approach will be used to test for statistically significant differences over time on primary and secondary outcomes between the two conditions. Hierarchical linear modelling (HLM) will be conducted for each continuous outcome, using a group × time interaction analysis. HLM allows the number of observations to vary between participants and effectively handles missing data. Time (linear and quadratic), treatment condition, and their interaction will be included in the models. Fixed effects parameters will be tested for intervention conditions, and time of assessments at 95 % confidence intervals. Level 1 of the model will represent within-patient change over time on the outcomes of interest, and level 2 of the model will include variables in which the patients are nested to provide better estimates of the within-patient change over time. Covariates will be added and model fit parameters will be used to determine the best fitting models for our data.

Analysis will focus on the primary outcome (PSC-35) and secondary outcomes between treatment and waitlist, with the main outcome point being post-intervention, relative to baseline. Completer analyses will also be conducted using only the data of participants completing the allocated intervention as planned. In addition to the primary analysis, subsequent exploratory analyses will be conducted to consider potential moderators and mediators on outcomes (independent from primary analyses). Across all analyses, two-tailed tests will be reported with *p* < 0.05. In parallel with quantitative analyses, information and observations on implementation will also be analysed to inform the dissemination of the programme.

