## Methods

### Design

The study is a single-blind type I hybrid effectiveness-implementation multi-site superiority RCT comparing the locally developed family intervention to a waitlist control group for families residing in vulnerable regions in North Lebanon and Beqaa governorates (including families of Syrian, Palestinian, and Lebanese backgrounds). Outcomes on family, adolescent, and caregiver measures will be assessed at baseline (T0) and post-intervention (T1), and at a 3-month follow-up for the treatment arm (T2). The primary outcome point is set as T1. The Standard Protocol Items: Recommendations for Interventional Trials (SPIRIT) is outlined in Fig. 1. A waitlist comparison condition was chosen in order to enable us to deliver a group-format version of the intervention with the control arm after T1 assessments are complete, to gather implementation data and experiences of this format.

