### Aims and hypotheses

The primary aim of the RCT is to assess the effectiveness of the family intervention on adolescent-reported symptoms of psychological distress at post-intervention. The secondary aim is to assess the effectiveness of the intervention using other measures of family functioning, parenting, and adolescent and caregiver mental health and wellbeing from pre- to post-intervention, and retention of effects in the treatment group at a 3-month follow-up timepoint. An additional aim is to explore possible treatment moderators (e.g. age, gender, past traumatic exposures, level of adversity, income). We will also explore whether treatment effects for adolescents and caregivers are mediated by improvements in (adolescent- and caregiver-reported) family functioning and (adolescent- and caregiver-reported) emotional regulation, and whether treatment effects for adolescents are mediated by improvements in caregiver outcomes.

Our hypotheses are:

i) Adolescents in families assigned to receive the family intervention will show significantly greater improvements in primary and secondary outcome measures compared to the waitlist group, at post-intervention.

ii) Caregivers in families assigned to receive the family intervention will show significantly greater improvements on caregiver-reported secondary outcome measures compared to the waitlist group, at post-intervention.

iii) These improvements for adolescents and caregivers will be maintained at the 3-month follow-up time point for the treatment condition.

iv) In the waitlist families who receive the intervention in a group format, we predict that there will be significant within-group improvements on outcome measures.

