### Intervention

The intervention is a six-session family intervention to be delivered by non-specialist facilitators. Family members will attend weekly two-hour long sessions together, and the programme will be delivered by one facilitator with one family. The first 1.5 h is delivered to the family unit. The final 0.5 h consists of a brief session for the caregivers only. After the 6th session, a booster session of 2 h will be provided after approximately 1 month. The programme was developed by the study team and partners through formative research ([name], [name], [name], [name], [name], [name], [name], [name], [name], [name], [name], [name], [name], [name], [name]: development of the ‘Sawa Aqwa (Stronger Together)’ Family Focused Psychosocial Support Program for at-risk adolescents in Lebanon, in preparation) and covers these main skills: identifying family values, goals, challenges, and strengths; emotional regulation; communication; problem management; managing disagreements; and positive parenting for adolescents. The programme is intended to be delivered face to face in a home visit or in a community centre; however, if safety concerns or restrictions related to COVID-19 prevent this, online modalities will be employed.

Families in the control group will receive the family intervention after T1 assessment. In order to further test the implementation model of the family intervention, the control group will receive a multi-family version of the intervention. Families will be assessed again after the intervention and will also be interviewed to identify implementation and acceptability differences between the versions. Other implementation data, like attendance, fidelity, and dropout, will be collected for both versions of the intervention.

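### The linear-and-quadratic time model cannot be fitted as written on the trial's visit schedule, and the T1 arm contrast that it can estimate is not named as the test

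*Protocol article*

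**What the plan says.** In the Analysis section, "Hierarchical linear modelling (HLM) will be conducted for each continuous outcome, using a group × time interaction analysis", and then "Time (linear and quadratic), treatment condition, and their interaction will be included in the models". The section adds that covariates will be added and that fit parameters will decide the final models. It sets the focus on treatment against waitlist, "with the main outcome point being post-intervention, relative to baseline".

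The Design section gives the schedule: outcomes "will be assessed at baseline (T0) and post-intervention (T1), and at a 3-month follow-up for the treatment arm (T2". It also fixes T1 as the primary outcome point. Hypothesis iii expects a plateau: "These improvements for adolescents and caregivers will be maintained at the 3-month follow-up time point for the treatment condition". The Intervention section adds one later waitlist assessment, made after that arm has received the multi-family programme: "Families will be assessed again after the intervention and will also be interviewed".

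**The concern.** A quadratic in time needs three time points. The waitlist arm supplies two to the randomised comparison, so a separate curve for each arm cannot be identified. When software meets an aliased design it drops a term or reports an error, and which term goes is often an accident of coding order. If the analyst then reads the primary result off one group × time coefficient, the number reported depends on that accident. Choosing the model by fit adds a second open choice. What is at stake is the single primary test, for which the protocol otherwise fixes a clear endpoint.

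**Working it through.** **Inputs.** T1 is about 10 weeks after T0 (Outcome measures). T2 is put at about 19 weeks in the same sentence that places it 12 weeks after T1, which gives 10 + 12 = 22; both values are used. The effect size of 0.25 is from Sample size, written as -0.25 SD because a lower PSC-35 score is better. The plateau is hypothesis iii. The flat waitlist and the 0.3 SD shared improvement used below are assumptions.

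**Rank.** Take columns 1, t, t², g, gt, gt², with g = 1 for treatment.
- T0 and T1 only: at t = 0 and 10, t² = 10t in both arms. That leaves four cell means: rank 4 of 6.
- Full schedule (waitlist T0, T1; treatment T0, T1, T2): t² - 10t is zero in every waitlist cell, so t² - 10t = gt² - 10gt throughout. There is one dependency among t, t², gt and gt²: rank 5 of 6.

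**What is estimable.** The null vector puts -10 on t, 1 on t², 10 on gt and -1 on gt². A contrast is estimable if its product with this vector is zero.
- gt alone: 10, not estimable.
- gt² alone: -1, not estimable.
- Arm difference in change from T0 to T1, 10·gt + 100·gt²: 100 - 100 = 0, estimable.

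**How far the single coefficient moves.** Let the treated means be 0, -0.25, -0.25 and the waitlist means 0, 0. The treated curve at + bt² satisfies 10a + 100b = -0.25 and a·T2 + b·T2² = -0.25.
- T2 = 22: b = 0.30/264 = 0.00114, a = -0.0364.
- T2 = 19: b = 0.225/171 = 0.00132, a = -0.0382.

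| Dropped term | gt per 10 weeks, T2 = 22 | gt per 10 weeks, T2 = 19 | T1 contrast |
|---|---|---|---|
| gt² (common quadratic kept) | -0.25 | -0.25 | -0.25 |
| t² (group × quadratic kept) | -0.36 | -0.38 | -0.25 |

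In the second row at week 22, 10·gt + 100·gt² = -0.364 + 0.114 = -0.25. The fitted contrast is right in both rows; only the lone coefficient moves.

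The same happens with no treatment effect. If both arms improve by 0.3 SD by T1 and the treated arm then stays level, a is scaled by 0.3/0.25 and the waitlist slope is -0.30 per 10 weeks. With t² dropped, gt per 10 weeks is -0.436 + 0.30 = -0.14 (week 22) or -0.458 + 0.30 = -0.16 (week 19). With gt² dropped it is 0.

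**Conditional case: both quadratic terms removed, T2 kept.** With complete data and a random intercept, each arm's slope is its least-squares slope.
- T2 = 22: treated slope = -2.667/242.67 = -0.0110 per week, or -0.11 at week 10.
- T2 = 19: -2.417/180.67 = -0.0134 per week, or -0.13 at week 10.

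The true value is -0.25. The fitted level difference at T1 is less affected, at 64% to 68% of the truth (-0.16 to -0.17). With no effect and the shared 0.3 SD improvement, the treated change is -0.132 (week 22) or -0.161 (week 19) against -0.30 for waitlist. That is a spurious +0.17 or +0.14 SD favouring waitlist.

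On T0 and T1 alone, linear time has rank 4 of 4 and the group × time term is exactly the T1 contrast.

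**The case against.** The strongest reply is that the primary effect is not lost. Dropping any one of the four aliased columns leaves the fitted means unchanged, and the T1 contrast is recovered every time. Categorical visit recovers it too, as does linear time on T0 and T1. The protocol writes interaction in the singular, so it may intend a common quadratic with group × linear only; that model has rank 5 of 5 and returns -0.25. All of this stands, and it limits the point to the stated coefficients and the unnamed contrast.

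A reader might infer that the planned analysis will give a wrong T1 effect through a linear model. The documents do not support that. They say that quadratic time will be included, no linear fallback is stated, and nothing says that T2 is pooled into the primary test. Fit-based selection makes that route possible, not planned. It is biased only if T2 is kept and the treated course is not linear.

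The waitlist's later assessment would bring the matrix to full rank, but it follows the group programme and cannot serve as control data. Nothing says that it will enter this model; hypothesis iv treats it as a within-group question. Coding time by actual assessment dates could identify curvature, but only weakly, from differences in timing between families.

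The protocol also defers detail to an analysis plan that is not shown. That plan may well settle the contrast, but to do so it has to replace or narrow a sentence that the protocol states outright.

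**Conclusion.** The point holds in limited form. As written, with both interactions and scheduled visits, the model is rank deficient by one on the full schedule and by two on T0 and T1. Its group × linear coefficient has no fixed meaning: -0.25, or -0.36 to -0.38, for the same truth. The T1-versus-baseline arm contrast remains estimable, so it would be wrong to say that the primary effect cannot be estimated. The defect is that the plan tests an interaction that the schedule cannot support and does not name the contrast that it can. The attenuation to -0.11 to -0.13 and the spurious +0.14 to +0.17 are conditional on a linear-only model that retains T2. They also rest on the plateau in hypothesis iii and, for the second pair, on the assumed 0.3 SD shared improvement.

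**What to change.** Delete linear and quadratic time from the Analysis section and treat visit as categorical. Fit the primary model to T0 and T1 from both arms with baseline adjustment, for example ANCOVA of T1 on T0 or a mixed model with equal baseline means. Name the arm difference at T1 as the sole primary test, and state that fit statistics do not choose this model.

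Analyse treatment-arm T2 and the waitlist's post-group assessment separately, as uncontrolled within-arm changes with confidence intervals. Reconcile the 19-week and 22-week timings for T2.

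The cost is analysis wording only, with no new data. It can be settled in the analysis plan that the protocol says will be signed before unmasking.

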### Randomisation

Randomisation will occur after T0 assessments are completed and will be stratified by site. The unit of randomisation will be families, and they will be randomly allocated to intervention or waitlist with a 1:1 ratio. The randomisation sequence will be computer-generated by a statistician located outside Lebanon, and independent of the study. It will be generated using Research Randomizer (randomizer.org [14]), a computer-based pseudo-random number generator using the “Math.random” method within the JavaScript programming language as the core methods for generating its random numbers. Families are randomised into the intervention group (see details in the “Intervention” section), or a waitlist condition, to receive the programme after post-intervention assessments (T1). They will receive the programme in a group format to assess the feasibility and acceptability of different delivery formats.

To ensure approximately equal randomisation in case smaller numbers of families per organisation are attained than planned, blocking will be used with block sizes unknown to the research team. An unblinded study coordinator will send participant lists (in order of baseline assessment completion date and time) to the independent statistician on a regular basis during the study enrolment period. The independent statistician will then match the randomly generated allocation sequence to the participant list and send this back to the unblinded study coordinator, who will then share participant allocations with implementing teams.

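### Model fit to the trial data decides the covariates in the confirmatory models, and the named group-by-time contrast uses baseline less efficiently than a fixed baseline-adjusted model would

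*Protocol article*

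**What the plan says.** The Analysis section sets the model for every continuous outcome: "Hierarchical linear modelling (HLM) will be conducted for each continuous outcome, using a group × time interaction analysis". The fixed effects are listed: "Time (linear and quadratic), treatment condition, and their interaction will be included in the models". Of the upper level it says that "level 2 of the model will include variables in which the patients are nested to provide better estimates of the within-patient change over time". The covariate rule follows: "Covariates will be added and model fit parameters will be used to determine the best fitting models for our data".

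The next paragraph places the primary contrast at T1, "with the main outcome point being post-intervention, relative to baseline", and describes moderator and mediator work as exploratory and separate from the primary analyses. The fit rule therefore belongs to the confirmatory models.

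The Randomisation section says: "Randomisation will occur after T0 assessments are completed and will be stratified by site". The Analysis section does not name site. It also plans baseline tests: "To determine comparability between the conditions at baseline, multiple planned comparisons will be conducted for continuous variables and chi-squared tests for categorical ones". A statistical analysis plan is to be signed before unmasking; it is not shown here.

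**The concern.** There are two issues.

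**The covariate set is not fixed.** The protocol states a rule for choosing covariates, and the rule needs the trial data. The models being compared contain treatment and its interaction with time, so comparing their fit as written needs outcomes and allocation together, and the treatment estimate is visible at each step. The chosen set can differ between outcomes. The protocol offers many candidates: the possible moderators listed under Aims and hypotheses (age, gender, trauma, adversity, income) and a 36-item inventory under Other measures. Some are measured after randomisation: daily stressors at T1 (Other measures) and other services used, asked at T1 (Other interventions). A fit criterion could admit these, and adjusting for a variable that treatment may have affected can bias the treatment effect.

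**Baseline is used inefficiently.** When T0 is one of the outcomes and the arms may differ freely at T0, the group-by-time term compares changes. Adjusting for baseline, or constraining the arms to a common baseline mean, gives a more precise estimate of the same treatment effect.

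**Working it through.** **Inputs from the protocol (Sample size, Randomisation).** Two-sided 5%, 80% power, effect size d = 0.25, 270 participants with T1 data, 1:1 allocation, so 135 per arm. The calculation is described as a two-group comparison at T1, with no baseline correlation. **Assumption:** the correlation r between T0 and T1 PSC-35 is not given, so a range is shown.

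**The plan's own figure.** With unit variance, n per arm = 2(1.96 + 0.842)²/0.25² ≈ 252, or 504 in total, not 270. With 135 per arm, the standard error is √(2/135) = 0.1217, the standardised effect is 0.25/0.1217 = 2.054, and power is Φ(2.054 − 1.96) = 54%. The mismatch is a separate matter. It enters here only because 270 is the sample size to which the efficiency comparison is applied.

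**Variance of the two contrasts.** For participants with T0 and T1, both variances set to 1:
- difference in change: V = 2(1 − r)
- baseline-adjusted T1 difference: V = 1 − r²
- ratio: 2(1 − r)/[(1 − r)(1 + r)] = 2/(1 + r), above 1 for any r below 1.

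Power = Φ(0.25/√(2V/135) − 1.96). At r = 0.5, change has V = 1.00 and power Φ(2.054 − 1.96) = 53.7%. Adjusted has V = 0.75 and power Φ(2.372 − 1.96) = 66.0%.

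| Assumed r | V change | V adjusted | Ratio | Power, change | Power, adjusted | Total N for 80%: change / adjusted |
|---|---|---|---|---|---|---|
| 0.4 | 1.20 | 0.84 | 1.43 | 46.6% | 61.1% | 604 / 422 |
| 0.5 | 1.00 | 0.75 | 1.33 | 53.7% | 66.0% | 504 / 378 |
| 0.6 | 0.80 | 0.64 | 1.25 | 63.2% | 72.8% | 402 / 322 |
| 0.7 | 0.60 | 0.51 | 1.18 | 75.5% | 82.0% | 302 / 258 |
| 0.8 | 0.40 | 0.36 | 1.11 | 90.1% | 92.8% | 202 / 182 |

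Below r = 0.5 the change contrast has V above 1, so it is less precise than the plain T1 comparison on which the sample size was based.

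**Unequal variances.** Write s0 and s1 for the T0 and T1 standard deviations. Change variance minus adjusted variance is (s0² + s1² − 2r·s0·s1) − s1²(1 − r²) = (s0 − r·s1)², which is never negative. Screening on the PSC-17 may narrow the T0 spread and shrink the gain, but in large samples change does not beat adjustment.

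**Type I error under covariate selection.** Simulation: 270 participants, three sites, change contrast, six pure-noise covariates, 2,000 runs per scenario (Monte Carlo standard error √(0.05 × 0.95/2000) ≈ 0.5 points), at r = 0.4 and 0.6:
- no covariates: 4.4% and 5.0%
- best AIC model, chosen without regard to the treatment result: 5.0% and 5.0%
- covariate set giving the smallest treatment p-value: 6.6% and 6.4%.

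**Site.** In the same simulation at d = 0.25, with site effects of −0.3, 0 and 0.3 SD at both T0 and T1, adding site moved power from 47.0% to 47.1% and from 65.2% to 65.2% for change, and from 60.0% to 60.7% and from 73.4% to 73.9% with baseline adjustment.

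**The case against.** The strongest reply is that the analysis plan, signed before unmasking, will name the covariates, and that an article may leave such detail to it. That would hold for an omission. Here the article states a rule, and a plan that followed it would still leave the primary model to be chosen with outcome data in hand. A plan that names the covariates would cure this, but it would have to depart from the sentence.

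Second, a difference in change is a valid, unbiased contrast in a randomised trial. This stands: the point is one of efficiency. Its size rests wholly on an assumed r, and at r = 0.8 the gain is under 3 points. The unnamed covariates could also include baseline, so the protocol does not rule out adjustment.

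Three stronger readings are tempting, and the document does not support them:
- *Site is omitted from the analysis.* Site is not committed to, but the level-2 wording and the open covariate list leave room for it. Site effects that are equal at T0 and T1 cancel from a change contrast, so no material loss follows. Site differences in change itself would matter more.
- *Fit-based selection seriously inflates type I error.* Selection on fit alone stayed at about the nominal level. Inflation needs a choice that follows the treatment result, which the protocol does not describe.
- *The baseline tests will choose the covariates.* The protocol gives their purpose as checking comparability and does not link them to any model. After proper randomisation such tests tell little about comparability, but they do not alter the primary result.

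**Conclusion.** The point holds as a free improvement, not a must-fix. The protocol makes the confirmatory covariates depend on fit to the trial data, without limiting them to baseline variables or committing to the stratification factor. The main harm is that the primary estimate is not fixed in advance. The type I error risk is modest (about 6.5% in the simulation when the covariate set with the smallest p-value was picked), and bias arises only if post-randomisation variables are admitted.

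The named model also gives up precision. Its variance is 1.43 times that of a baseline-adjusted analysis at r = 0.4, 1.33 times at 0.5 and 1.11 times at 0.8, which costs about 14, 12 and 3 percentage points of power with 270 participants at d = 0.25. These figures assume equal T0 and T1 variances, complete T0 and T1 data, no other covariates and an r that the protocol does not give.

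**What to change.** Replace the covariate sentence with one prespecified model for every outcome. Either of these would do:
- the T1 value adjusted for the baseline value of the same measure and for site; or
- a longitudinal model that constrains the arms to a common baseline mean, with site.

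Any further covariates should be baseline variables named before unmasking. Confine fit-based selection to analyses labelled exploratory, and state that the baseline comparisons do not drive covariate choice.

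The cost is wording in the protocol and analysis plan. Site and the baseline outcome measures are already recorded, so no new data or participants are needed.

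### The supplementary completer analysis can select only in the treated arm, so its T1 contrast with the waitlist is no longer protected by randomisation

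*Protocol article*

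**What the plan says.** The Analysis section makes intention to treat the main approach: "An intent-to-treat analysis approach will be used to test for statistically significant differences over time on primary and secondary outcomes". The contrast is treatment against waitlist, "with the main outcome point being post-intervention, relative to baseline". It then adds a second population: "Completer analyses will also be conducted using only the data of participants completing the allocated intervention as planned".

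What there is to complete differs by arm. For treated families, "The intervention is a six-session family intervention to be delivered by non-specialist facilitators", with weekly sessions that precede T1. For the others, "Families in the control group will receive the family intervention after T1 assessment"; the Design and Randomisation sections give the same timing, and the waitlist version is a multi-family group format.

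The same section calls the moderator and mediator analyses exploratory. It attaches no such label to the completer analysis, and it applies two-tailed testing at the 0.05 level to all analyses. Further detail is deferred: "All analyses will be detailed in a statistical analysis plan, which will be signed before unmasking the study data set".

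**The concern.** Restricting to completers keeps a comparison fair only if the same kind of family is removed from both arms. Here that cannot happen. No waitlist family can have failed, by T1, to complete a programme it has not yet been offered. The retained treated families are those able and willing to attend week after week, and they may differ from the rest in stability, motivation or distress. Their counterparts in the waitlist arm cannot be identified and stay mixed with everyone else.

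At stake is the interpretation of a supplementary result. A completer contrast is naturally taken as the effect of receiving the programme, but this one combines any such effect with differences in who stays. As worded, it would carry significance tests without a caution.

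**Working it through.** **1. Which families the filter can remove.** Set the Analysis sentence beside the Intervention and Randomisation sections.

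| Arm | Programme before T1 | Can be a non-completer at T1? |
|---|---|---|
| Treatment | six weekly family sessions | yes |
| Waitlist | none | no |

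On a more literal reading, the allocated intervention of a waitlist family is the later group programme. Both arms would then be filtered, but on different programmes, and the waitlist arm on behaviour that follows its T1 outcome. Randomisation does not protect the contrast on that reading either.

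**2. Size under no true effect, comparison at T1 only.** The article has no figure to reproduce: it gives neither a completion rate nor a link between completion and outcome. Both are assumed below. Its planned effect of 0.25 (Sample size section) serves only as a yardstick.

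Let c be the share of treated families completing, and r the correlation between a normal latent propensity to complete and the outcome (SD 1). Then

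bias = r × φ(z) / c, where z is the normal quantile at 1 − c.

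| c | φ(z)/c | r = 0.1 | r = 0.2 | r = 0.3 |
|---|---|---|---|---|
| 0.6 | 0.3863/0.6 = 0.644 | 0.064 | 0.129 | 0.193 |
| 0.7 | 0.3477/0.7 = 0.497 | 0.050 | 0.099 | 0.149 |
| 0.8 | 0.2800/0.8 = 0.350 | 0.035 | 0.070 | 0.105 |

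The range is 0.035 to 0.193 SD, or 14% to 77% of 0.25.

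**3. A second route.** Let g be the gap in mean outcome, in SD, between families who would and would not complete. Then bias = (1 − c) × g. With c = 0.7 and g = 0.3 (assumed), bias = 0.3 × 0.3 = 0.09 SD.

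Take 270/2 = 135 families per arm at T1, so 94.5 completers on average. The standard error is √(1/94.5 + 1/135) = 0.134, the shift is 0.09/0.134 = 0.67 standard errors, and the two-sided false-positive rate is 10.3% instead of 5%. A simulation of 20,000 trials with these inputs, in which completers have the lower distress, gave:
- all treated against all waitlist: 0.00
- treated completers against all waitlist: −0.09
- treated completers against would-be waitlist completers: 0.00

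The error comes from the one-sided filter.

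**4. Effect of the planned model.** Steps 2 and 3 ignore baseline. For a difference in change from T0 to T1, with gaps g0 at baseline and g1 at T1, the bias is (1 − c) × (g1 − g0). It is zero if the gap is constant, undiminished if there is no gap at baseline, and of opposite sign if the gap narrows. The figures above are therefore illustrations, not estimates for the planned model.

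**5. The alternative estimate.** With no programme access on the waitlist before T1, the CACE estimate is the intention-to-treat difference divided by the proportion of the treated arm counted as receiving the programme. It requires that families counted as non-receivers gain nothing, so the definition of receipt matters. Suppose 70% complete and gain 0.25, and the other 30% attend some sessions and gain half of that, 0.125 (assumed):
- intention-to-treat difference = 0.7 × 0.25 + 0.3 × 0.125 = 0.2125
- receipt defined as completion: 0.2125/0.7 = 0.304, too high by 0.054 against the completers' 0.25
- receipt defined as any session: 0.2125/1 = 0.2125, the correct mean effect among attenders

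**The case against.** The strongest reply is that this is a supplementary analysis beside intention to treat, of a kind that is common and widely understood to be non-randomised, and that its details belong in a statistical analysis plan that is not shown. The first part stands: a reader might infer that the trial's main conclusion is compromised, and the documents do not support that. The second part stands for the session threshold, whose absence from an article is no fault. It does not remove the point, because the article itself fixes the population, and a plan that carries out that sentence inherits the asymmetry whatever session count it chooses.

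Two further objections hold. First, a reader might infer that the completer result will overstate benefit, by up to 77% of the planned effect. The article documents neither a direction nor the inputs. More distressed families may be keener to attend, improving families may stop early, and a model relative to baseline may absorb part of the selection. Second, a reader might infer that the completer result would be put forward in place of a weak main result. Nothing in the article says so, and whether the sample size is adequate is a separate question that this point does not need.

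It is also fair to say that a CACE analysis has a bias of its own if partial attenders benefit, as step 5 shows. That argues for a broad definition of receipt, not for the completer contrast.

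**Conclusion.** The point holds for the supplementary completer analysis only. Its T1 contrast is not a randomised comparison on either reading of the sentence; this follows from the article's own timing and needs no assumption. How far the result would be off, and in which direction, is not documented. The 0.04–0.19 SD range rests on assumed completion of 60–80% and an assumed correlation of 0.1–0.3 in a comparison at T1 alone, and it shrinks to the extent that baseline carries the selection. There would be no bias if all treated families completed or if completion were unrelated to the outcome analysed. This is a cheap improvement, not a threat to the primary inference.

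**What to change.** Estimate the effect of receiving the programme by a CACE analysis at T1:
- randomised arm as the instrument, with the primary model's covariates
- all randomised families included, with missing T1 data handled as in the primary analysis (the article allows for 30% attrition)
- receipt defined before unmasking from the facilitators' session checklists, counting sessions before T1
- attendance at any session as the main definition, so that the exclusion restriction is plausible, and a higher session threshold as a sensitivity analysis

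If the completer analysis is kept, label it non-randomised and exploratory.

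The cost is a sentence or two of analysis wording; the Fidelity and Intervention sections show that attendance is already recorded. The downsides are the exclusion restriction, which must be stated, and a wider interval. Treating the proportion receiving as known, the interval is about 1/0.7 = 1.43 times the intention-to-treat interval if 70% count as receivers, and 1/0.9 = 1.11 times if 90% do (both proportions assumed).
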